#### Secondary outcomes

Table 1 gives an overview of the secondary outcome measures in the effect evaluation. For these outcome measures, at discharge from GR, mean differences between the intervention and control group will be assessed.

**Table 1 Tab1:** Secondary outcome measures in the FIT-HIP trial

Domain	Assessment	Description	Time point(s)
Physical functioning and activity	Barthel index [40]	Activities in daily living. Measures (in)dependence in personal care (eating, dressing, bathing, going to the toilet) and mobility.	BA, DA, FU1, FU2
	Functional ambulation categories [41]	Evaluates ambulation ability, describing the degree of human support the person needs when walking.	BA, DA, FU1, FU2
	10 meter walk test [42, 43]	Assesses walking function/speed.	BA, DA
	Activity restriction due to fear of falling	Assessed in questionnaire, asking if participant has experienced restriction of activity due to the fear of falling.	BA, DA, FU1, FU2
Falls, complications and health care service usage	Falls (and fall-related injury)	Number of fall incidents and medical attention required as a result of the fall. Assessed using monthly fall calendars.	BA, DA, FU1, FU2
	Complications during GR	Number and type of complication occurring during GR. Assessed by elderly care physician (ECP) in monthly calendars.	Until discharge from GR
	Hospital (re)admission	Number of hospital readmissions and days in hospital. Assessed by ECP in monthly calendars during GR and questionnaire at discharge from GR. Assessed by participants using questionnaire in FU.	DA, FU1, FU2
	Mortality		DA, FU1, FU2
	Healthcare consumption after discharge	Number of contacts with health and community services. Assessed by participants using questionnaire in FU.	FU1, FU2
Other outcome characteristics of GR	Duration of admission to GR	Number of days admitted to GR. Assessed by ECP (questionnaire).	DA
	Total amount of therapy in GR	Number of hours of physiotherapy and of contact with ECP. Assessed by physiotherapists in weekly calendars and by ECP in monthly calendars.	Until discharge from GR
	Discharge location	Location of the residence to which participant is discharged after GR. Assessed by ECP (questionnaire).	DA
Health-related quality of life	EuroQol 5D (EQ5D) [44]	The three-level EuroQol 5D (EQ-5D) is a standardised instrument for measuring generic health status. It can be used for calculating quality adjusted life years (QALYs), for the economic evaluation.	BA, DA, FU1, FU2
Participation	The Utrecht Scale for the Evaluation of Rehabilitation-Participation. (USER-P) [45]	Assesses (limitations in) participation in relation to health problems.	BA, FU1, FU2

*BA* baseline assessment (pre-intervention), *DA* discharge assessment (post-intervention), *FU1* follow-up 1 assessments, 3 months after discharge from GR, *FU2* follow-up 2 assessments, 6 months after discharge from GR, *ECP* elderly care physician, *GR* geriatric rehabilitation (multi-disciplinary inpatient rehabilitation programme), *EQ-5D* EuroQol 5D, *USER-P* Utrecht Scale for the Evaluation of rehabilitation - participation

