**Methods/design:**

This multicentre cluster randomised controlled trial will be conducted among older patients with hip fracture and fear of falling who are admitted to a multidisciplinary inpatient geriatric rehabilitation programme in eleven post-acute geriatric rehabilitation units. Fifteen participants will be recruited from each site. Recruitment sites will be allocated by computer randomisation to either the control group, receiving usual care, or to the intervention group receiving the FIT-HIP intervention in addition to usual care. The FIT-HIP intervention is conducted by physiotherapists and will be embedded in usual care. It consists of various elements of cognitive behavioural therapy, including guided exposure to feared activities (that are avoided by the participants). Participants and outcome assessors are blinded to group allocation. Follow-up measurements will be performed at 3 and 6 months after discharge from geriatric rehabilitation. (Cost)-effectiveness and feasibility of the intervention will be evaluated. Primary outcome measures are fear of falling and mobility.

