### Secondary objectives

To compare the effect of the FIT-HIP intervention with usual care with respect to improving the degree of independence in ADL (Barthel index), ambulation ability (Functional Ambulation Categories) and walking speed.To compare the number of fall incidents, mortality, hospital (re)admission and psychosocial functioning (social participation after discharge from GR, measured by the Utrecht Scale for Evaluation of Rehabilitation-subscale Participation; and quality of life, measured by the EuroQol 5D) between the FIT-HIP intervention and usual care.To examine the feasibility of the FIT-HIP intervention for participants and therapists conducting the FIT-HIP intervention.To perform an economic evaluation, consisting of a cost analysis and cost-utility analysis, comparing the FIT-HIP intervention with usual care. Costs will be measured from a healthcare perspective.

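### The single rule for secondary outcomes, a mean difference at discharge, cannot be applied to two of the 14 outcomes, does not fit several others, and leaves the effect evaluation without a stated contrast at follow-up

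*Protocol article*

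**What the plan says.** The text introducing Table 1 (Protocol article, Secondary outcomes) gives one contrast for everything in the table: "For these outcome measures, at discharge from GR, mean differences between the intervention and control group will be assessed".

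Table 1 then lists 14 outcomes with their own time points. Participation, measured by USER-P ("Assesses (limitations in) participation in relation to health problems"), is scheduled at baseline, follow-up 1 and follow-up 2. The row headed "Healthcare consumption after discharge" is described as "Number of contacts with health and community services. Assessed by participants using questionnaire in FU", and is scheduled at follow-up 1 and 2 only.

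Secondary objectives promises a between-group comparison of "social participation after discharge from GR, measured by the Utrecht Scale for Evaluation of Rehabilitation-subscale Participation". The abstract confirms the schedule: "Follow-up measurements will be performed at 3 and 6 months after discharge from geriatric rehabilitation".

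Data analyses assigns multilevel models to continuous outcomes and logistic GEE to dichotomous ones, without naming a time point. Economic evaluation and Data analyses together plan a comparison of costs and QALYs over the 6 months after discharge. Duration of the FIT-HIP intervention says that the stay is set individually, averages 6 weeks, and is recorded in days.

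**The concern.** The introductory sentence is a rule, and a rule can be tested by following it. Followed as written, it asks for a discharge contrast on outcomes that have no discharge value, and for a mean where no mean exists. It also names only one of the three post-baseline assessments.

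Two things are at stake. First, where the rule fails or is silent, the analyst has to choose the time point and effect measure later. For the seven outcomes with three post-baseline time points, that leaves open which result is reported as the secondary finding. This matters here because part of the intervention acts after discharge: the relapse prevention plan is meant for the home situation and the telephone booster comes six weeks after discharge, so a discharge contrast cannot capture the booster.

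Second, falls and readmissions up to discharge accumulate over a stay that differs between patients. Duration of admission is itself a Table 1 outcome, so the trial allows that it may differ between arms. A difference in mean counts could then reflect time at risk and not the event rate.

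**Working it through.** **Step 1: time points.** Table 1 set against the rule, with BA = baseline, DA = discharge, FU1 and FU2 = 3 and 6 months after discharge:

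| Outcomes | Time points | Discharge contrast possible? |
|---|---|---|
| Barthel index, FAC, activity restriction, falls, EQ-5D | BA, DA, FU1, FU2 | yes |
| Hospital (re)admission, mortality | DA, FU1, FU2 | yes |
| 10 meter walk test | BA, DA | yes |
| Duration of admission, discharge location | DA | yes by timing |
| Complications, total therapy | until discharge | yes by timing |
| USER-P | BA, FU1, FU2 | no |
| Healthcare consumption | FU1, FU2 | no |

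Count: 5 + 2 + 1 + 2 + 2 + 1 + 1 = 14 outcomes. The rule cannot be computed for 2 of 14.

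**Step 2: follow-up.** Outcomes collected at FU1 and FU2: 5 + 2 + 1 + 1 = 9 of 14. Seven of these also have a discharge value; the other two are USER-P and healthcare consumption. For none of the nine does Secondary outcomes or Data analyses state an effect contrast at FU1 or FU2. EQ-5D and healthcare use enter a 6-month between-arm comparison through QALYs and costs. For USER-P, Secondary objectives states the intention to compare after discharge, but the rule does not carry it out.

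**Step 3: effect measure.**
- Discharge location is a set of categories, so a mean is undefined. The same holds for the type component of "Number and type of complication occurring during GR".
- Mortality is dichotomous. Data analyses gives it logistic GEE, which yields an odds ratio. The two sections name different effect measures for the same outcome.
- Falls ("Number of fall incidents and medical attention required as a result of the fall") and readmissions are counts. A difference in mean counts can be computed, but up to discharge it depends on time at risk.

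**Step 4: size of the length-of-stay effect.** The reference stay is 6 weeks = 42 days (Duration of the FIT-HIP intervention). The difference in mean stay between arms, d, is not given and is assumed over a range. With the same daily event rate r in both arms, expected counts are r × 42 and r × (42 + d). The relative shift is (42 + d)/42 − 1 = d/42, and r cancels.

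- d = 0: 0/42 = 0%
- d = 3: 3/42 = 7%
- d = 7: 7/42 = 17%
- d = 14: 14/42 = 33%

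The plan gives no figure of its own on this point to reproduce.

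**The case against.** The strongest reply is that this is a loose summary sentence in a condensed article. It does not say that discharge is the sole time point or the mean difference the sole measure; a reader who takes it as exclusive is adding that. Healthcare consumption is labelled as occurring after discharge in the same table, and the objective places participation there too, so the intent can be recovered. That is fair as far as it goes. But the sentence covers every Table 1 outcome, and for two of them it is wrong as written. An analysis plan could work around it without making the protocol text right.

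A reader might also infer that the follow-up data go unused. The documents do not support that: costs and QALYs are compared over 6 months, drawing on EQ-5D and healthcare use including hospitalisation. What is missing is narrower, namely a stated effect-evaluation contrast at FU1 and FU2.

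A reader might infer that mortality has no suitable analysis. It has one, in the logistic GEE; the defect is that the two sections disagree. Nor is it an error that the article names no ordinal model for FAC, no time-to-event model for mortality and no repeated-measures model. Those are choices that an analysis plan may hold.

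On length of stay, the article records days in rehabilitation and allows them as a confounding variable. That use is optional and does not turn a count into a rate. It is also true that nothing in the documents predicts a difference in stay between arms, and that at zero difference the distortion is zero. After discharge the planned windows have the same length in both arms, so this part of the point concerns mainly the period up to discharge.

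**Conclusion.** The point holds in this form. The rule contradicts Table 1 for two of 14 secondary outcomes, one of which serves a named objective. It has no meaning for discharge location, disagrees with Data analyses for dichotomous outcomes, and leaves nine outcomes collected at FU1 and FU2 without a stated effect contrast there. These statements rest on the documents alone.

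The length-of-stay figures (0% to 33%) rest on assumed arm differences of 0 to 14 days, a 42-day reference and equal event rates. They show how the mean count responds to length of stay and do not predict what the trial will find.

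It would go too far to conclude that the trial cannot answer its participation question. The USER-P data are scheduled and the intention to compare them is stated; the contrast sentence simply points to the wrong visit. The primary outcomes are not affected. This should be corrected before analysis, and the correction is easy.

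**What to change.** Replace the sentence that introduces Table 1 with a statement of time point and effect measure by outcome:

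- USER-P and healthcare consumption: between-arm contrasts at FU1 and FU2.
- All other outcomes: contrasts at discharge (or over the stay, where recorded until discharge) and, where collected, at FU1 and FU2.
- Continuous outcomes: the multilevel model already named in Data analyses. Dichotomous outcomes, including mortality: the logistic GEE already named there, with its own effect measure in place of a mean difference.
- Falls and readmissions: event rates per days observed, adjusted for clustering by rehabilitation unit.
- Discharge location: compared as a category.

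All the data needed are already scheduled, including days in rehabilitation. The cost is a change of wording and a little more analysis work.

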#### Additional variables

Table 2 gives an overview of the additional variables assessed in this trial.

**Table 2 Tab2:** Additional variables assessed in the FIT-HIP trial

Domain	Assessment	Description	Time point(s)
Socio-demographics	Age, gender, marital status, type of residence prior to hip fracture		BA
General health and physical functioning	Functional comorbidity index (weighed) [46]	Assesses 18 comorbid conditions and their effect on physical functioning.	BA
	Medication use	Number and type of medication used by participants. Assessed by ECP (questionnaire).	BA, DA
	Assistive walking device	Type of assistive walking aid, used for indoor and outdoor usage. Assessed by questionnaire.	BA
	Use of formal care (home care) and informal care (given by relatives/volunteers)	Assessed by questionnaire.	BA, FU1, FU2
	Previous fall frequency	Number of falls in 6 months prior to hip fracture.	BA
	Handheld grip strength	Evaluated with dynamometer.	BA
	Nutritional status: Body Mass Index	Calculated by dividing bodyweight in kilograms by length in meters squared.	BA, DA
	Numeric Pain Rating Scale (NPRS) [47]	Assesses intensity of pain on an 11-point scale (0 –10).	BA, DA, FU1, FU2
Hip fracture (related) characteristics	Type of fracture, operation, weight-bearing capacity	Assessed by ECP (questionnaire).	BA
	Duration of hospital admission due to hip fracture	Number of days in hospital.	BA
	Complications during hospital admission due to hip fracture	Number and type of complications. Assessed by ECP (questionnaire).	BA
Neuropsychological factors	Mini Mental State Examination (MMSE) [48, 49]	Screens for cognitive disorders and dementia	BA
	Geriatric Depression Scale, 8-item (GDS-8) [50]	Short adapted version of the GDS-30. Developed to screen depression in nursing home population.	BA
	Hospital anxiety and depression scale – subscale anxiety (HADS-A) [51]	Screens for anxiety.	BA
	Utrecht Coping List; subscales active and passive coping. (UCL) [52]	Assesses coping mechanism. Questionnaire assesses how a person deals with problematic situations in general.	BA
	Pittsburgh Rehabilitation Participation Scale [53]	Participation/motivation for physiotherapy (PT) during GR.	During every session of PT until discharge

*BA* baseline assessment (pre-intervention), *DA* discharge assessment (post-intervention), *FU1* follow-up 1 assessment, 3 months after discharge from GR, *FU2* follow-up 2 assessment, 6 months after discharge from GR, *ECP* elderly care physician, *NPRS* numeric pain rating scale, *MMSE* mini mental state examination, *GDS-8* geriatric depression scale, 8-item, *HADS-A* hospital anxiety and depression scale – subscale anxiety, *UCL* Utrecht’s coping list, *PT* physiotherapy

### Process evaluation

To determine the feasibility of the FIT-HIP intervention, a process evaluation will be conducted in accordance with the theory of Saunders et al. [37] Using a mixed-method approach, information about reach, fidelity, exposure, satisfaction and barriers for applying the programme will be assessed. Table 3 gives an overview of the measurement instruments used to collect these data.

**Table 3 Tab3:** Outcome measures of the FIT-HIP process evaluation

Component and definition	Operationalisation	Measurement instruments									
		SLog	QpD	QpF1	QpF2	Ip	It	Qt	BLog	Sq	D
Reach											
Proportion of the intended target population that participated in the programme	Refusal and dropout rate. Reasons for withdrawal									+	+
Fidelity											
Extent to which the elements of the intervention were implemented as planned	Per therapy session: registration of which intervention components were performed	+									
	Per therapy session: reasons for deviation from individual FIT-HIP therapy plan	+									
	Reasons for deviation from protocol						+				
Dose received - Exposure											
Extent of participants’ active engagement in and receptiveness to the programme	Per therapy session: extent of active engagement in therapy	+									
	In general: use of relapse prevention plan (Staying Active Plan)			+	+				+		
Dose received - Satisfaction											
Satisfaction of participants and therapists with the programme	Overall opinion about the intervention		+	+	+	+	+	+			
	Opinion about the value of the intervention		+	+	+	+	+	+			
	Opinion about the value of the main elements of the intervention		+	+	+	+	+				
	Experienced burden		+			+	+				
Barriers											
The extent to which problems were encountered while applying the programme	Barriers in applying the (individual components of the) intervention.						+				
	Suggestions for improvement		+	+	+	+	+	+			
	Recruitment procedures						+				+
	Maintaining participant engagement						+				+

*SLog* physiotherapist session log, *QpD* evaluation questionnaire filled in by participant at discharge from GR, *QpF1* evaluation questionnaire filled in by participant at follow-up 1 (3 months after discharge from GR), *QpF2* evaluation questionnaire filled in by participant at follow-up 2 (6 months after discharge from GR), *Ip* Interview with participant, *It* interview with physiotherapist and psychologist, *Qt* evaluation questionnaire filled in by GR team members: elderly care physician, nursing staff and psychologist, *BLog* booster log, registration of telephonic booster, *Sq* screening questionnaire filled in at admission to GR, *D* data recorded by research assistants during study period

#### Therapist data

In the intervention arm of this trial, physiotherapists will register per session which elements of the intervention were conducted, reasons for deviating from the individual FIT-HIP therapy plan and the duration of the therapy sessions, using weekly calendars as session logs. Also, for each therapy session, the Pittsburgh Rehabilitation Participation Scale is filled in as a measure of the extent of active engagement of the participant in the therapy. At the end of the study, the physiotherapists and psychologists conducting the intervention will be invited to take part in qualitative group interviews to discuss in detail their satisfaction with the (components of the) intervention, experienced barriers applying the intervention and suggestions for improvement. Also, matters concerning participant recruitment and maintaining participant engagement will be discussed.

Other members of the GR team (the elderly physician and nursing staff) will be approached to fill in a short evaluation questionnaire about their general opinion of the intervention and to assess to what extent the individual FIT-HIP therapy plans were routinely discussed in the GR team.

#### Participant data

All participants in the intervention arm of this trial will receive evaluation questionnaires at discharge from GR and at follow-up (3 and 6 months after discharge from GR). In these questionnaires, information on experienced benefits and burden of the intervention, and suggestions for improvement of the intervention, will be assessed. In addition, qualitative interviews will be held with a (random) subgroup of the participants, to gain more insight into these matters.

### Economic evaluation

The economic evaluation consists of a cost analysis and a cost-utility analysis, both with a 6-month time horizon after discharge from GR. Costs will be measured from a healthcare perspective. In the cost-utility analysis, the difference in healthcare costs between the strategies will be compared to the difference in Quality-Adjusted Life Years (QALYs, calculated using the 3-level Dutch EQ-5D tariff [38] and the visual analogue scale for health). Estimated healthcare costs will include the costs of the FIT-HIP intervention (estimated from the study registration) and other healthcare utilisation (estimated using quarterly questionnaires filled in by the patients). Other healthcare utilisation will include care provided by general practitioners, consultations of medical specialists and paramedics, home care, informal care, hospitalisation, and residential care. A cost-price analysis will be performed for the FIT-HIP intervention; other healthcare items will be valued using standard prices.

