### Duration of the FIT-HIP intervention

The FIT-HIP intervention, integrated in the usual care, will be conducted during the entire period that the participant is admitted to GR. The duration of the inpatient GR is determined for each participant individually, and is therefore variable. On average, the duration of admission to GR for rehabilitation after hip fracture is 6 weeks. During the trial, the following is registered: i) total duration of GR in days, ii) number of therapy sessions during GR, iii) duration of therapy sessions, and iv) (in the intervention group) performance of the individual components of the FIT-HIP intervention; all these elements can be used as confounding variables in the final outcome analyses.

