### Effect evaluation

#### Primary outcome

1. Mean difference in the Tinetti Performance Oriented Mobility Assessment (POMA) score [32, 33] at discharge from GR (or at a maximum of 3 months after admittance to GR), compared between FIT-HIP intervention and usual care. The POMA is a measure of mobility function (gait and balance).

2. Mean difference in the Falls Efficacy Scale International (FES-I) score [34–36] at discharge from GR (or at a maximum of 3 months after admittance to GR), compared between FIT-HIP intervention and usual care. The FES-I is a measure of fear of falling.

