### Data analyses

Differences between the intervention and control group in characteristics of participants at baseline will be tested with chi-square tests for categorical variables, Mann-Whitney *U*-test for continuous variables with skewed distributions, and one-way ANOVA for normally distributed continuous variables. Given the hierarchical data structure, multilevel analyses will be used for continuous outcomes, and logistic Generalized Estimated Equation (GEE) analyses for dichotomous outcomes. Logistic GEE is preferred to logistic multilevel analyses because of the instability of the latter. Analyses will be based on an intention-to-treat principle and the level of significance will be set at *p* < 0.05. Missing data will be handled as missing (no imputation). Multilevel analyses will be performed with MLwiN. All other analyses will be performed with IBM SPSS statistics.

With regard to the qualitative data (assessed for the process evaluation), these will be analysed by means of coding techniques based on transcriptions of the qualitative interviews. In the economic evaluation, group averages will be compared using unequal-variance t-tests, according to the intention-to-treat principle. Costs will be compared to QALYs using net-benefit analysis. Multiple imputation will be used to account for missing values. Sensitivity analysis will be performed on the time horizon (base case 6 months vs. 12 months) and the utility measure (base case Dutch EQ-5D tariff vs. visual analogue scale for health).

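### The economic window opens at discharge, so FIT-HIP's inpatient cost is charged while the inpatient stay and its QALYs appear uncounted, and the 12-month scenario outruns follow-up

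*Protocol article*

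**What the plan says.** The Economic evaluation section of the protocol article describes a cost analysis and a cost-utility analysis, "both with a 6-month time horizon after discharge from GR". On costs it says "Estimated healthcare costs will include the costs of the FIT-HIP intervention (estimated from the study registration"), and adds a list of other items: "Other healthcare utilisation will include care provided by general practitioners, consultations of medical specialists and paramedics, home care, informal care, hospitalisation, and residential care". These other items are to be estimated from questionnaires that patients complete each quarter. Table 1 places healthcare consumption at the two follow-ups only (FU1 and FU2, 3 and 6 months after discharge).

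The intervention itself "will be conducted during the entire period that the participant is admitted to GR" (Duration of the FIT-HIP intervention); a single telephone booster follows 6 weeks after discharge.

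Under Data analyses, the plan is: "Sensitivity analysis will be performed on the time horizon (base case 6 months vs. 12 months"). The Abstract states "Follow-up measurements will be performed at 3 and 6 months after discharge from geriatric rehabilitation". No later contact appears in Table 1 or Table 2.

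**The concern.** Discharge comes after allocation, and its timing may differ between arms. Table 1 itself lists duration of admission and amount of therapy among the outcomes to be compared. If the economic clock starts there, costs and effects cover different periods. The cost of an inpatient intervention enters the comparison, but the inpatient days it might lengthen or shorten do not, and neither does health-related quality of life during those days. A true difference in the inpatient phase, in either direction, would not reach the incremental cost or the incremental QALYs.

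At the other end, a 12-month horizon is longer than any participant is followed. Multiple imputation is the only method named for incomplete economic data, and it has no observed values to draw on beyond FU2. The scenario would therefore depend on extrapolation, which the text does not say.

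**Working it through.** The horizon is a stated choice, so there is no calculated figure to reproduce. The check is arithmetic on the timeline.

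Inputs from the protocol article:
- Mean stay: "On average, the duration of admission to GR for rehabilitation after hip fracture is 6 weeks" (Duration of the FIT-HIP intervention), which is 42 days or 1.38 months.
- Latest discharge assessment: "at discharge from GR (or at a maximum of 3 months after admittance to GR") (Primary outcome). This caps the assessment, not the stay. It serves here as a second example, with discharge at 3 months.
- Last measurement: 6 months after discharge (Abstract; Table 1), about 182.6 days.
- Assumption: the baseline assessment is taken as roughly the date of admission.

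**1. Does a 6-month base case fit a clock that starts at admission?** The span from admission to FU2 is stay + 6 months.
- 6-week stay: 1.38 + 6 = 7.38 months.
- Discharge at 3 months: 3 + 6 = 9.0 months.

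Neither is 6 months, so the base case named under Data analyses fits only a clock that starts at discharge.

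**2. Share of the observed span before the window opens.**
- 6-week stay: 42 / (42 + 182.6) = 18.7%.
- Discharge at 3 months: 3 / 9 = 33.3%.

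**3. Shortfall of the 12-month scenario.**
- Counted from discharge: 12 − 6 = 6.0 months, or 50% of the horizon.
- Counted from admission, 6-week stay: 12 − 7.38 = 4.62 months (38.5%).
- Counted from admission, discharge at 3 months: 12 − 9 = 3.0 months (25%).

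The shortfall from admission would vanish only with a 6-month stay.

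**4. What is counted on each side of discharge.**

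| Item | Before discharge | After discharge |
|---|---|---|
| FIT-HIP cost | counted | counted (telephone booster) |
| Rehabilitation stay | days recorded, not in the cost list | not applicable |
| Healthcare consumption questionnaire | none scheduled | FU1, FU2 |
| EQ-5D | measured at baseline and discharge | measured at FU1, FU2 |
| QALYs in the stated window | no | yes |

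**5. Illustration of the QALY part.** The documents give no utility difference, so these are assumed constant differences between arms. The QALYs missed during a 6-week stay are difference × 1.38 / 12; over the 6 months after discharge they are difference × 0.5.

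| Assumed difference | Missed during 6-week stay | 6 months after discharge |
|---|---|---|
| 0.02 | 0.0023 | 0.010 |
| 0.05 | 0.0057 | 0.025 |
| 0.10 | 0.0115 | 0.050 |

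The missed part is 1.38 / 6 = 23% of the counted part in each row. No comparable figure can be given for cost, because the documents contain no price for a rehabilitation day and no expected difference in stay.

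**The case against.** The strongest reply is that the article never says pre-discharge costs or QALYs are excluded. The phrase about the horizon could mark where it ends. Table 1 schedules EQ-5D at baseline and discharge and links the instrument to the economic evaluation. The FIT-HIP cost is itself mostly a pre-discharge cost. The cost list is not said to be exhaustive, and residential care might be stretched to cover a stay in a nursing-home unit. Item-level costing may also stand in a fuller plan.

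Part of this stands: the exclusion is inferred, not stated. It is still the natural reading. A base case of 6 months does not fit a span of 7.4 months or more, and reading residential care as the rehabilitation stay sits badly with a clock that starts at discharge and with consumption data collected only afterwards.

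A reader might infer more than the documents support:
- That deaths before discharge are dropped. The article does not say so; mortality is recorded at discharge and intention-to-treat is applied to the economic evaluation.
- That FIT-HIP will change length of stay, or that the omission is worth a given sum. Nothing predicts such a change or prices it, and 19% of the time is not 19% of the incremental result.
- That the 12-month scenario has no data at all. Half of it is observed when counted from discharge, and more when counted from admission. Extrapolation is a legitimate way to vary a horizon, and a model for it may exist elsewhere.

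**Conclusion.** The point holds in a limited form. On the natural reading, the economic evaluation charges an intervention delivered mainly during the stay while leaving the stay and its QALYs outside the window. About 19% of the period from admission to FU2 is lost at the mean stay of 6 weeks, and a third if discharge falls at 3 months. These are shares of time, not estimates of bias; the effect on the cost-utility result depends on unknown differences between arms and could go either way.

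The mismatch of the 12-month scenario is firmer, since it exceeds planned follow-up under either clock. What is wrong is that the text does not identify it as extrapolation, not that a model is absent from a condensed article.

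The primary outcomes and the sample size are untouched.

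**What to change.** - Start costs and QALYs at the baseline assessment.
- Value the recorded rehabilitation days and therapy hours at standard prices. FIT-HIP is given within physiotherapy sessions, so its time must not be counted twice; nor should therapy hours be added if the day price already contains them.
- Compute QALYs as the area under the curve from EQ-5D at baseline, discharge, FU1 and FU2, with zero utility after death. This also settles how deaths before discharge enter.
- Drop the 12-month scenario, or label it a modelled extrapolation and state its assumptions.
- As a minor matter, reconcile informal care, which is listed among the costs, with the stated healthcare perspective.

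The cost is a change of analysis wording and slightly more analysis work. Table 1 already provides EQ-5D at all four time points, days in rehabilitation, therapy hours and mortality, so no new data collection is needed.
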